### Concealment mechanism {16b}

The randomisation schedule will be embedded within the online database (REDCap [52]) which will automatically assign the participant after they complete the baseline survey to either the intervention or control arm ensuring allocation concealment. User permissions in REDCap will be restricted so that only the trial statistician has access to the schedule.

#### Implementation {16c}

A statistician not involved in the recruitment of participants or data collection will generate the randomisation schedule and upload it to the trial online database. Research assistants within the trial will enrol participants (defined as receipt of the study consent form, either in person or via post) and then randomise them using the randomisation module in the REDCap database.

## Assignment of interventions: blinding

### Who will be blinded {17a}

It is not possible to blind the participants or their GPs to their arm as they will receive their personal risk of CRC derived from the PRS if they are in the intervention arm. The control arm will receive standard cancer prevention information as an attention control and usual care from their GP with regard to their cancer screening.

Research staff who randomise the participant and return the PRS and screening recommendations to participants in the intervention arm also cannot be blinded. However, staff who conduct the questionnaire follow-up with the participants over the phone will be blinded. Staff who analyse the data will be blinded (arms will be designated randomly at that point as A and B).

### Procedure for unblinding if needed {17b}

As participants cannot be blinded and there must be some unblinded research staff to deliver the intervention to participants, there does not need to be a procedure for unblinding.

## Data collection and management

### Plans for assessment and collection of outcomes {18a}

#### Primary outcome

The primary outcome is the proportion of participants who have had risk-appropriate CRC screening at 12 months’ follow-up. The appropriate type and frequency of screen will be determined by participant’s level of CRC risk as follows:

For those aged 50 years and over:*Average-risk category*: for participants whose 10-year absolute risk of colorectal cancer is less than 4% based on their PRS, family history, age and sex (intervention only) and who do not fall into the moderate risk category of the 2017 NHMRC-endorsed Australian guidelines [5] (both trial arms), iFOBT every 2 years is considered risk-appropriate screening.*Moderate-risk category*: for participants whose 10-year absolute risk of colorectal cancer is greater than or equal to 4% based on their PRS, family history, age and sex (intervention only), or they had a self-reported family history of CRC (both trial arms) that places then in the moderate risk category of the 2017 Australian guidelines [5], risk-appropriate screening is colonoscopy every 5 years.

For those aged under 50 years:*Average-risk category*: for participants whose 10-year absolute risk of colorectal cancer is less than 1% based on their PRS, family history, age and sex (intervention only) and do not fall into the moderate risk category of the 2017 NHMRC-endorsed Australian guidelines [25] (both trial arms), risk-appropriate screening is no screening until aged 50 years.*Moderate-risk category*: for participants whose 10-year absolute risk of colorectal cancer is greater than or equal to 1% based on their PRS, family history, age and sex (intervention only), or they had a self-reported family history of CRC (both trial arms) that placed then in the moderate risk category of the 2017 Australian guidelines [5], risk-appropriate screening is iFOBT every 2 years until aged 50 years.

Exceptions to these rules are:*Moderate- or average-risk category*: If a participant had a history of colorectal adenomas or sessile serrated lesions, whether and when a colonoscopy should be repeated is based on the 2017 Australian guidelines [53] The timing and mode of follow-up test resulting from previous adenomas/sessile serrated lesions would take precedence over the screening recommended by standard national guidelines (control arm) or by the PRS (intervention arm).*Average-risk category and aged 50 years or over*: Those whose last test was a colonoscopy (for any reason), where the colonoscopy results do not require colonoscopic follow-up, are due an iFOBT after 4 years.

CRC screening behaviour will be collected via self-report by participants (via questionnaires at baseline, 1 month, 6 months and 12 months), as well as objective sources of data (GP record, Victorian Admitted Episodes Dataset (VAED), Medicare Benefits Schedule (MBS) and the National Bowel Cancer Screening Program (NBCSP)).

Screening prior to enrolment in the study as well as participant’s CRC risk category determines the timing of risk-appropriate screening within the 12-month follow-up period. All data sources with information on type of screening (self-report, GP record, VAED, MBS and NBCSP) will be used to determine screening prior to enrolment of participants. Self-reported events will be included, as this reflects what information a GP would use if considering screening to order in a standard consultation.

Objective data sources based on administrative data sources (GP record, VAED, MBS and NBCSP) will be used to determine whether a screening event has occurred within the 12-month follow-up period. Self-reported events will not be included, unless no objective data are available.

A Clinical Consensus Group (consisting of gastroenterologists and GPs, blinded to trial arm allocation) will review participants with complex past histories and use all available data sources to determine what risk-appropriate screening would be consistent with NHMRC surveillance and screening guidelines.

#### Secondary outcomes

Data for secondary outcomes will be collected primarily from participants’ questionnaires at 1, 6 and 12 months post-intervention delivery.Participants will be asked to state their CRC risk perception numerically, on a scale from 0 to 100, and comparatively to an ‘average’ person, from 1 — much lower — to 7 — much higher [46].The Cancer Worry Scale [47] is a validated, 6-item scale measuring anxiety about the risk of CRC. Each item is rated on a 1–4 scale (not at all or rarely to almost all the time) and then summed for a total.The Preventative Health Model [48] is an 18-item, validated scale, answered on a five-point Likert scale from strongly disagree to strongly agree. It measures known predictors of CRC screening behaviour in five subscales: salience and coherence (4 items), response efficacy (2 items), cancer worries (2 items), social influence (4 items) and self-efficacy (6 items). Each subscale is summed for a total.CRC screening intentions to undertake screening or discuss screening with their GP will be measured with a five-point Likert scale from strongly disagree to strongly agree.The cost of the SCRIPT intervention, health service utilisation and health care costs will be calculated based on the assessment of GP consultations, colonoscopy services, iFOBT, and associated pathology services obtained from audit of GP records, and data from the MBS, VAED and NBCSP records. Any other associated changes in health care utilisation will be captured through access to participants’ MBS and GP record data. Indirect costs will not be included.Five-year impact on risk-appropriate screening behaviour and health service utilisation will be measured but only utilising objective, administrative data. Impact on screening behaviour will be assessed as per the primary outcome.

### Plans to promote participant retention and complete follow-up {18b}

Prior to consent, participants will be advised that they can withdraw from the study at any time without giving a reason. If they withdraw, there will be no further contact from the study, including follow-up questionnaires. Any data already collected will be included in analyses and objective screening data will still be collected as this does not require contact with the participant. Participants who withdraw can also choose to withdraw all their data that they have previously provided, except when their data have been processed and analysed. If this is the case, any unprocessed data that has not been included in an analysis at the time of withdrawal will be destroyed and their data excluded from the analysis.

Reminders will be made to participants regarding each follow-up questionnaire. Telephone contact will initially be attempted, with the offer to complete the questionnaire over the phone. If the participant cannot be contacted via phone, email and/or SMS reminders will be sent. A maximum of two reminders (i.e. successful contact via phone or sending of an email or SMS) will be made; then, this questionnaire is considered lost to follow-up. Participants will still be sent subsequent questionnaires unless explicitly withdrawing from the trial.

### Data management {19}

Data will be collected, managed and stored according to the study’s data management plan, developed in accordance with the University of Melbourne’s Research Data Management Policy and Research Code of Conduct. A REDCap database will be used to collect and store data, only accessible by authorised and trained researchers. REDCap is a password-protected online database. The REDCap database has mandatory data entry fields to reduce missing data, range checks for the data values and branching questions. Before randomisation, REDCap provides a pop-up for researchers to doublecheck data entry of the stratifying variable. All paper-based data will be entered directly into REDCap and these will be stored securely in an office within the Victorian Comprehensive Cancer Centre in a locked file cabinet. All data will only be accessible to researchers listed on ethical approvals.

### Confidentiality {27}

Prior to consent, any information about potential participants will not leave the patient’s general practice and is not retained by researchers.

In accordance with the University of Melbourne’s Research Data Management Policy and Research Code of Conduct, participants’ research data will be stored on University managed and/or sanctioned storage infrastructure. Data will be secured via a personal login and data elements restricted by role at the direction of the chief investigator. Participant contact information (address, phone number and email address) will be stored on REDCap only, and access will be restricted to members of the research team who require it for study-related contact. This restriction will be built into REDCap user roles. Each participant will be given a unique de-identified study code and all data extracted from the REDCap database will only contain this study code. Paper-based data will be destroyed using confidential waste management services 5 years after the publication of the results.

Individual-level data will be made available to external researchers on a case-by-case basis. This excludes data provided by external organisations (Services Australia (MBS data), AIHW (NBCSP data) and DHHS (VAED data)), as well as data collected from GP records. It also excludes identifying data and only age brackets rather than dates of birth will be provided. Sharing of this data will only take place after ethical approval.

### Plans for collection, laboratory evaluation and storage of biological specimens for genetic or molecular analysis in this trial/future use {33}

DNA will be collected with ORAcollect®-DNA OCR-100 saliva collection kits (DNA Genotek, Ottawa, ON, Canada). Genotyping will be conducted by Genetic Technologies using their GeneType for Colorectal Cancer test (https://www.gtglabs.com/colorectal-cancer). DNA samples will be processed and genotyped according to their National Association of Testing Authorities (NATA)-approved processes and any excess DNA disposed of according to the same guidelines. Participant DNA will not be retained for future use.

## Statistical methods

### Statistical methods for primary and secondary outcomes {20a}

The primary analysis will be based on the intention to treat principle where all randomised participants will be analysed in their allocated study arm. Baseline characteristics of the two arms will be summarised using descriptive statistics. Possible differential attrition will be assessed by comparing baseline characteristics of those who withdraw against those who remain in the study. For the primary outcome analysis, a generalised linear model with the identity link function and binomial family will be used to estimate the absolute difference in the proportion of participants who have had risk-appropriate CRC at 12 months between intervention and control arms. We will also estimate the odds ratio using logistic regression. In all regression analysis, the randomisation stratification factor, general practice, will be included as fixed effect. The absolute (between-arm difference in the proportions) and relative (odds ratio) estimated effect sizes will be presented with their respective 95% confidence interval (CI), and the *p*-value will be estimated using logistic regression. Comparisons between arms on continuous secondary endpoints will be undertaken using a linear mixed-effects model that includes arm (intervention and control), general practice and time (baseline, 1, 6 and 12 months) as fixed effects and individuals as random effect, with two-way interaction between arm and time, except baseline where study arm means will be constrained to be equal. Differences between arms on binary secondary endpoints will be estimated using logistic regression using generalised estimating equations with robust standard errors to allow for the repeated outcome measures on individuals (1, 6 and 12 months), adjusting for general practice. All analyses will be conducted in Stata 17 [54].

The health economic analysis combines a within-trial and modelled analysis of the cost-effectiveness of implementing the genomic test. The within-trial analysis will consider the costs per appropriately screened individual in the two arms. The modelled analysis will consider how the incremental cost per appropriately screened individual might vary given differences in population incidence of the SNP variants, as well as potential variations in test sensitivity/specificity, and compliance with screening recommendations. Within-trial costs will be estimated based on data obtained from general practice, Medicare, NBCSP and VAED records. Mean estimates of costs will be used, and confidence intervals will be generated by resampling (bootstrap) techniques. Results for both analyses will be presented in terms of an incremental cost-effectiveness ratio as the cost per risk-appropriate screened participant.

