### Sample size {14}

We used the results of the CRISP trial to inform our sample size calculations for this trial (paper under review, *Med. J. Aust.*). The original sample size of 218 participants for the grant application was based on a 20% difference between the intervention and control arms, assuming 25% in the control arm and 45% in the intervention arm, with 10% attrition at 12 months. However, in the CRISP trial, we found 40% had risk-appropriate screening in the control arm and 60% in the intervention arm of those due screening at 12 months for participants aged 50 years and older. The primary outcome had less than 5% missing data as it was derived from multiple data sources (such as GP record, Victorian Admitted Episodes Dataset (VAED), Medicare Benefits Schedule (MBS), the National Bowel Cancer Screening Program (NBCSP)) and did not rely only on self-report from a returned questionnaire. Furthermore, our original sample size calculation assumed all participants would be due a CRC screening test, as would be expected for participants aged above 50 years old based on current guidelines and the eligibility criteria. However, for participants aged 45 to 49 years, appropriate screening will be defined as no CRC screening if classified as having average CRC risk and iFOBT if they are classified as moderate CRC risk. Hence, to ensure that we had sufficient power to detect a difference appropriate CRC screening between the arms, we revised our sample size to allow for an attenuation in the intervention effect, explained as follows.

We estimated that 25% of the trial sample will be aged 45–49 years old, of which 90% will be at average risk and 10% at moderate risk [50]. We conservatively assumed that 95% of those aged 45 to 49 years in the average risk group will be appropriately screened in both trial arms (i.e. no CRC screening); those identified as moderate risk, we assumed that 70% in the intervention arm and 10% in the control arm would be appropriately screened (i.e. iFOBT screening). Thus, for those aged 45–49 years, the expected between-arm difference in appropriate screening would be 6% (92.5% intervention vs 86.5% in the control arm). We also assumed that for participants aged 50 years and older who were due a CRC screening test in the next 12 months, 60% would be appropriately screened in the intervention arm and 40% in the control arm (paper in submission).

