Thus, we revised the sample size to detect a between-arm difference of 17% (68% vs 51%, after taking a weighted average of the proportions aged above or below 50 years). To detect this effect size, with 80% power and a two-sided 5% significance level, we require a total sample size of 274 participants at baseline (137 participants per arm), allowing for 5% of the primary outcome data to be missing.

This is an additional 56 participants to the trial from the original sample size calculations provided in the grant proposal and Trials registry. This sample size also provides 90% power (5% significance level) to detect a 20% between-arm difference for appropriate screening for participants aged 50 years and older (60% in the intervention and 40% in the control group, 5% missing data).

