### Methods for additional analyses (e.g. subgroup analyses) {20b}

Sensitivity analyses will adjust for pre-specified baseline variables, such as risk group at baseline and whether recruitment occurred in person or via telehealth, in the regression models for the primary and secondary outcomes.

Sensitivity analyses are also planned to explore the impact on the intervention effect when using different data sources to define the primary outcome. For instance, defining risk-appropriate screening based on information from participant self-report and GP records on past screening at baseline (e.g. previous findings at colonoscopy, date of the last iFOBT). This is to emulate the real-world setting where the GP would not have access to additional administrative data during the consultation to determine what type of CRC screening was due (MBS, VAED). Sensitivity analyses will also test the robustness of the result to variations in the underlying assumptions and inputs to the health economic analysis.

Further additional analyses, including sensitivity, subgroup and supplementary analyses, will be described in a detailed statistical analysis plan (SAP) that will be made available prior to the analysis of the primary outcome.

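### The primary model adjusts for general practice only; on the plan's own rates, adding age band (45–49 vs 50 or older) would gain about 5 points of power without new data

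*Protocol article*

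**What the plan says.** The section on statistical methods for primary and secondary outcomes {20a} fixes the primary analysis. For the absolute difference, "a generalised linear model with the identity link function and binomial family will be used"; the odds ratio and the p-value come from logistic regression. On covariates it says: "In all regression analysis, the randomisation stratification factor, general practice, will be included as fixed effect". No other term is named.

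Under additional analyses {20b}: "Sensitivity analyses will adjust for pre-specified baseline variables, such as risk group at baseline", followed by recruitment mode. Randomisation {16a} is stratified by practice alone.

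The sample size section {14} supplies the rates. "We estimated that 25% of the trial sample will be aged 45–49 years old". For that band "the expected between-arm difference in appropriate screening would be 6% (92.5% intervention vs 86.5% in the control arm"). For those aged 50 and older it assumes 60% against 40%. The two bands are then averaged to "detect a between-arm difference of 17% (68% vs 51%, after taking a weighted average of the proportions aged above or below 50 years").

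**The concern.** Success means a different thing in the two age bands. For most participants under 50 it means having no test, which nearly everyone achieves. From 50 it means completing a test, which a minority of controls are expected to do. The expected control rates are therefore 86.5% and 40%. Age is settled at eligibility, before randomisation, so it could enter the model without difficulty of principle. Leaving it out means that between-band variation stays in the error of the treatment comparison. At stake is precision in a trial sized with almost no margin.

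**Working it through.** **Inputs, all from Sample size {14} unless stated.** Share aged 45–49: 25%. Rates at 45–49: 92.5% vs 86.5%. Rates at 50 and older: 60% vs 40%. Two-sided 5%, 80% power, 5% missing. Allocation 1:1 {16a}. Six to ten practices {9}. The document gives no practice effect, so none is assumed.

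**1. The plan's own figure.** A two-proportion calculation for 68% vs 51% (pooled variance, no continuity correction) needs 130 per arm; 130/0.95 = 136.8, so 137 per arm and 274 in total. The stated size reproduces, and 130 analysed per arm gives 80.1% power.

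**2. Unrounded rates.** Intervention: 0.25 × 0.925 + 0.75 × 0.60 = 0.68125. Control: 0.25 × 0.865 + 0.75 × 0.40 = 0.51625. The difference is 16.5 points, not 17, and the same formula gives 77.8% power.

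**3. Strength of age band.**
- Odds ratio for age, control: (0.865/0.135)/(0.40/0.60) = 9.6.
- Odds ratio for age, intervention: (0.925/0.075)/(0.60/0.40) = 8.2.
- Odds ratio for arm, pooled over age: (0.68125/0.31875)/(0.51625/0.48375) = 2.0.
- Share of outcome variance: age 0.1875 × (0.895 − 0.50)²/(0.59875 × 0.40125) = 12%; arm 0.25 × 0.165²/(0.59875 × 0.40125) = 3%.

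**4. Variance of the risk difference.**
- Ignoring age: 0.68125 × 0.31875 + 0.51625 × 0.48375 = 0.4669; SE = √(0.4669/130) = 0.0599.
- Within bands: 0.25 × (0.925 × 0.075 + 0.865 × 0.135) + 0.75 × (0.24 + 0.24) = 0.4065; SE = √(0.4065/130) = 0.0559.
- Ratio 0.4065/0.4669 = 0.871, a 13% reduction.

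Analytic power, with the null variance used for the test in both cases, goes from 77.8% to 83.0%.

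**5. Simulated power of the logistic p-value.** 260 analysed, practice as fixed effects, 6,000 runs per row.

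| Practices | Practice only | Practice + age band |
|---|---|---|
| 6 | 78.6% | 83.3% |
| 8 | 78.2% | 83.3% |
| 10 | 78.4% | 83.9% |

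A separate simulation with 8 practices gave about 77% and 82–83%. Type I error was about 5.5–6% with or without the age term.

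**6. Sensitivity to the share under 50.**

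| Share aged 45–49 | Analytic | Simulated |
|---|---|---|
| 15% | 83.2% → 86.3% | 85.1% → 87.5% |
| 20% | 80.6% → 84.7% | 81.8% → 85.5% |
| 35% | 71.9% → 79.1% | 72.4% → 78.9% |

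Allowing for simulation error, the gain is about 2 to 4 points at 15% and about 7 at 35%.

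**7. Why age cannot simply join the identity-link model.** The assumed differences are 6 and 20 points, and an additive model forces one common value, weighted by inverse variance. The weights are 0.25/0.18615 = 1.343 (under 50) and 0.75/0.48 = 1.5625 (50 and older). The common difference is (1.343 × 0.06 + 1.5625 × 0.20)/2.9055 = 13.5 points, with SE 1/√(130 × 2.9055) = 0.0515 and power about 75%. In 1,500 simulated trials a basic iterative fit converged with all fitted probabilities inside 0–1 in about 5% of runs, against 99.8% without age. A constrained fit would converge more often but would still shift the estimate.

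**8. Standardising the age-adjusted logistic model** kept the difference at 16.5 points, with empirical SE about 0.057 against 0.060 without age. The odds ratio moved from about 2.06 to about 2.30 (averages over simulated trials).

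**The case against.** Adjusting for the sole stratification factor is a valid intention-to-treat analysis, and the sample size was computed for an unadjusted comparison, so sizing and analysis agree. That stands. A reader might infer that the practice-only estimate is biased, or that omitting age is what takes power below 80%. Neither is supported: the small shortfall comes from rounding 16.5 points to 17.

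A reader might also count chance age imbalance as a second harm. The between-arm difference in the share under 50 has SD √(2 × 0.25 × 0.75/130) = 5.4 points. Multiplied by the mean between-band gap, (0.465 + 0.325)/2 = 0.395, this contributes a variance of about 0.00045. The precision loss in step 4 is 0.0599² − 0.0559² = 0.00046. They are the same loss, and the unadjusted confidence interval already covers it.

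The gain rests on planning guesses and is modest if few under-50s enrol. That also stands, hence the range.

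The list of sensitivity covariates is open-ended and the unseen SAP may include age there. But the items the protocol defers are additional analyses, adherence adjustment and missing data; the covariates of the primary model are fixed in {20a}.

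Finally, one might infer that the baseline risk group is arm-dependent and would bias the sensitivity analysis. The protocol does not define that covariate, and DNA and family history are collected in both arms, so a common definition is available. What can be said is that the only risk categories the protocol defines, under outcome assessment {18a}, use the PRS in the intervention arm only.

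**Conclusion.** The point holds as a missed efficiency gain, not an error. On the plan's rates, age band is by far the strongest predictor it quantifies. Adding it to the logistic model gains about 5 points of power (from about 77–79% to 82–84%) at a 25% share under 50. This rests on the assumed rates in both bands, 5% missing data and no practice effect on the outcome.

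It would go too far to call the gain free. No extra participants or data are needed, but the risk-difference model has to be replaced and the odds ratio changes meaning. The change is worth making because the planned analysis has so little margin, and the benefit is largest where power is weakest, at a high share of under-50s.

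**What to change.** Before any unblinded analysis, pre-specify one primary logistic model with arm, practice and age band at enrolment (45–49 vs 50 or older). Take the p-value and odds ratio from it, and obtain the risk difference with its 95% CI by marginal standardisation from the same model, in place of the identity-link binomial model. State that the odds ratio is conditional on practice and age band. The practice-only analysis can stay as a sensitivity analysis.

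In the sensitivity analyses {20b}, define any baseline risk-group covariate identically in both arms, for example as the NHMRC family-history category recorded before randomisation.

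Cost: a wording change in the analysis plan, one covariate already collected and one standardisation step in Stata.

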#### Secondary outcomes

Difference between the SCRIPT intervention arm and standard cancer prevention information arm for the following secondary outcomes:Perceived personal risk of CRC, using mean absolute risk estimates and proportions estimating themselves as average, higher than average and lower than average at 1, 6 and 12 months, will be measured using existing validated items [46]Mean cancer-specific anxiety at 1, 6 and 12 months on the Cancer Worry Scale [47]Mean scores of predictors of CRC screening behaviour (salience and coherence, response efficacy, cancer worries, social influence, self-efficacy) at 1, 6 and 12 months taken from the Preventative Health Model [48]Proportions with CRC screening intentions at 1 and 6 months based on the Theory of Planned Behaviour [49]Mean costs of delivering the SCRIPT intervention (pre- and post-test consultations, buccal kits and SNP test) and the control consultation, as well as health service utilisation and direct health care costs at 12 monthsRisk-appropriate screening behaviour after 5 years

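### The model for continuous secondary outcomes states a person random effect as its only source of within-person correlation, so standard errors of visit-specific arm differences can be wrong if correlations are unequal

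*Protocol article*

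**What the plan says.** The protocol article, section Statistical methods for primary and secondary outcomes {20a}, sets out the model: "Comparisons between arms on continuous secondary endpoints will be undertaken using a linear mixed-effects model". Besides arm, the terms listed are "general practice and time (baseline, 1, 6 and 12 months) as fixed effects and individuals as random effect". The sentence then lets the arm effect vary by visit and ties the arms together at the start: "with two-way interaction between arm and time, except baseline where study arm means will be constrained to be equal". The result is a separate arm difference at 1, 6 and 12 months, each adjusted for baseline through the constraint.

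The next sentence gives the binary secondary outcomes a different treatment: "logistic regression using generalised estimating equations with robust standard errors to allow for the repeated outcome measures on individuals". Nothing equivalent is stated for the continuous model. The software is fixed: "All analyses will be conducted in Stata 17".

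The outcomes concerned are the numerical risk-perception score, the Preventative Health Model subscales and the worry score, for example "Mean cancer-specific anxiety at 1, 6 and 12 months on the Cancer Worry Scale". The later sections on additional analyses {20b} and on non-adherence and missing data {20c} defer several items to a statistical analysis plan. The main model for these outcomes is not among the items they name.

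**The concern.** A random intercept with independent, equal-variance residuals forces the same variance at all four visits and the same correlation between any two of them. Two features of this trial make that doubtful. The gaps between successive visits are 1, 5 and 6 months, and repeated scores may be less alike over longer gaps. In the intervention arm a personal risk estimate is delivered between baseline and the first follow-up, which may loosen the link between baseline and all later scores.

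Because baseline means are constrained equal, each arm difference is adjusted for baseline using the one common correlation. If the true correlation between baseline and a given visit differs from it, the model-based standard error at that visit is wrong, and so are the interval and p-value.

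The Discussion gives these outcomes an explanatory role, particularly if the primary comparison shows no clinically important difference, and expects them to feed an implementation strategy.

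**Working it through.** **The plan's own figure.** The protocol gives no standard deviation, correlation or standard error for the continuous outcomes. The only figure available is the primary sample size, 68% against 51% "with 80% power and a two-sided 5% significance level".

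n per arm = [1.96√(2p̄(1−p̄)) + 0.8416√(p₁(1−p₁)+p₂(1−p₂))]² / (p₁−p₂)², with p̄ = 0.595

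= [1.96√0.48195 + 0.8416√0.4675]² / 0.0289 = (1.3607 + 0.5754)² / 0.0289 = 129.7, so 130.

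Dividing by 0.95 gives 136.8, so 137 per arm and 274 in total, as stated. This does not bear on the secondary model beyond setting the scale.

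**What the stated model implies.** With a person effect of variance σ_b² and independent residuals of variance σ_e², every visit has variance σ_b²+σ_e² and every pair of visits has correlation ρ = σ_b²/(σ_b²+σ_e²).

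**Standard error of the arm difference at visit t.** With complete data and baseline means constrained equal, the estimate is D_t − ρD₀, where D is the raw difference in arm means. Let r_t be the true correlation between baseline and visit t. With equal variances, in units of 2σ²/n:

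- variance the model reports: 1 − ρ²
- true variance: 1 + ρ² − 2ρr_t

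These agree only if r_t = ρ. The fitted ρ tends to the mean of the six pairwise correlations. The actual type I error of a nominal 5% test is 2{1 − Φ(1.96 × model SE / true SE)}. For unequal variances (pattern e), ρ is the mean covariance c̄ over the mean variance s̄². The model reports s̄²(1−ρ²), and the truth is s_t² + ρ²s₀² − 2ρc₀ₜ.

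**Assumed patterns** (none comes from the protocol):

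| Pattern | Model SE / true SE at 1, 6, 12 months | Type I error at 1, 6, 12 months |
|---|---|---|
| (a) exchangeable | 1.00, 1.00, 1.00 | 5.0, 5.0, 5.0% |
| (b) 0.70 − 0.01 per month of lag | 1.07, 1.01, 0.95 | 3.6, 4.8, 6.3% |
| (c) 0.75 − 0.02 per month of lag | 1.14, 1.02, 0.91 | 2.6, 4.6, 7.4% |
| (d) first-order autoregressive by visit, 0.7 | 1.13, 0.94, 0.85 | 2.7, 6.6, 9.6% |
| (e) correlation 0.6, SDs 1, 1, 1.1, 1.2 | 1.08, 0.98, 0.90 | 3.4, 5.4, 7.9% |
| (f) baseline to follow-up 0.45, between follow-ups 0.7 | 0.91, 0.91, 0.91 | 7.5, 7.5, 7.5% |

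Two rows by hand:

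- Pattern (d): ρ = (3×0.7 + 2×0.49 + 0.343)/6 = 0.5705. The model variance is 1 − 0.3255 = 0.6745. At 12 months r = 0.343, so the true variance is 1.3255 − 0.3914 = 0.9341, and √(0.6745/0.9341) = 0.85. At 1 month r = 0.7, so the true variance is 1.3255 − 0.7987 = 0.5268, and the ratio is 1.13.
- Pattern (f): ρ = (3×0.45 + 3×0.7)/6 = 0.575. The model variance is 0.6694 and the true variance is 1.3306 − 0.5175 = 0.8131, so the ratio is 0.91 at every visit.

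Other patterns widen the picture. Exponential decay 0.8×0.95^lag gives 1.21, 1.01 and 0.90. Equal correlation 0.6 with a follow-up SD of 1.15 gives 0.97 at each visit (5.8%).

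**Simulation check.** I used pattern (d) with 137 per arm, dropout of 5, 10 and 15% completely at random, 400 trials and a REML random-intercept fit. The SE ratios were 1.18, 0.94 and 0.83, and the rejection rates were 2.0, 6.8 and 11.5%. With 400 trials the 11.5% carries a Monte Carlo standard error of √(0.115×0.885/400) = 1.6 points. The direction agrees with the formula.

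**What an unstructured covariance changes.** It gives nominal error in large samples. Its own standard error is only 0 to 4% below the true standard error of the random-intercept estimate, so the gain is validity rather than precision.

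**The case against.** The strongest reply is that the article does not rule anything out. It does not say that the person effect is the sole dependence structure, that residuals are independent with constant variance, or that standard errors are model-based. Stata can add a residual structure or robust standard errors to a person random effect, and an unseen analysis plan may do so. Naming robust standard errors for the estimating equations may simply reflect routine practice. Random-intercept models with a constrained baseline are also a common specification.

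Much of this stands. A reader might infer that the trial has committed itself to compound symmetry with model-based standard errors, but the text is silent rather than explicit on that. A reader might also infer that the intervals will be too narrow at 12 months and too wide at 1 month. The protocol supplies no correlations, so neither is established: pattern (a) shows no error, and pattern (f) reverses the 1-month direction.

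What does not stand is that this is only an omitted detail. The model is written out here, with one device for within-person dependence. The items openly passed to the analysis plan are additional, adherence and missing-data analyses. A sentence that can be implemented exactly as written, and would then lack protection, is worth completing.

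**Conclusion.** The point holds as a minor one. As written, the stated model gives correct standard errors for the visit-specific arm differences only if variances and correlations are equal across baseline, 1, 6 and 12 months, and the design gives reason to doubt that.

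In patterns (b) to (f) the 12-month standard error is about 5 to 15% too small, with type I error of about 6 to 10%. Milder departures do less. At 1 month the standard error is 7 to 14% too large in (b) to (e) and 9% too small in (f). All these sizes rest on assumed correlations and variances, on large-sample formulas with complete data, and on model-based standard errors being used.

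The effect is confined to standard errors, intervals and p-values of the continuous secondary outcomes. With complete data, or data missing completely at random, the arm differences themselves stay unbiased. The primary analysis and the 274 participants are not touched.

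**What to change.** Keep the constrained-baseline model and its visit-specific arm differences. State that within-person dependence will be modelled by an unstructured residual covariance over the four visits, in place of the random intercept. Name the fallback in advance: if that model does not converge, fit the random intercept with robust standard errors clustered on the participant.

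The cost is one sentence and one model option. Four visits need 4 variances and 6 covariances, 10 parameters in place of 2, which a sample of 274 can support. The downside is a possible convergence failure, which the named fallback covers. If correlations do turn out to be exchangeable, little is lost. If the analysis plan already specifies either approach, a cross-reference from this section is enough.
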